### Case finding and screening

"Case finding" patients will be identified during the patient interview using the following 4 questions:

1. Do you have any complaints about your memory?

2. Have you mentioned these to you GP?

3. If not, have you been intending to tell your GP?

4. Have you sought treatment or taken any remedies such as herbal medications or vitamins specifically for you memory? Please give details.

If questions 2, 3 or 4 are answered in the affirmative, the patient will be considered as a "case finding" patient. Patients identified as having possible or probable dementia on the GP baseline audit will also be considered as a "case finding" patient. All other patients will be identified as "screening" patients - that is, patients who would not receive a cognitive function test unless the GP decided to screen all patients aged over a certain age.

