### Sample size

It was calculated that 45 patients with dementia in each group (Waitlist and Intervention) would give a power of 0.9 to detect a 7% difference between the change in pre and post scores on any of the four domain scales of the WHOQOL-BREF with a type 1 error of .05. The population standard deviation used is 18.5 [32] and the Pearson correlation coefficient between the pre and post scores for both groups is assumed to be 0.7, based on pilot data available from the University of Melbourne.

The hierarchical nature of the study design will probably lead to some within cluster correlations and the greatest impact of this is likely to be associated with patients clustered within a GP practice. Clustering within each GP may be discounted, as it is anticipated that most GPs will have less than five patients with dementia in this study. Assuming an intra-class correlation coefficient of 0.05 and an average cluster size of 5 patients with dementia in a practice, this gives a design effect of 1.45 and a total sample size of 54 patients per group. We will therefore allow for 56 patients with dementia in the waitlist group and 112 in the intervention group to allow for comparison of outcomes between the waitlist and intervention groups overall. This sample size also allows comparison of "case finding" and "screening" patients and their support persons within the group. It is assumed that about 50% of participants will be screening and 50% case finding. Thus, we aim to recruit 168 participants with dementia overall. Based on a dementia prevalence of approximately 10% in over 75 year old Australians [37], we aim to recruit a total of 2,000 participants.

For the GDS, following the same set of assumptions and approach as for the WHO QOL-BREF (power, type 1 error and correlations), 45 patients in both the Intervention and Waitlist groups would allow detection of an average difference in the change in pre and post scores of 0.9 points on the 15 point GDS, using a standard deviation of 2.39 [28]. The cluster effect would be the same as for the WHOQOL-BREF.

For an estimate of test re-test reliability on the GPCOG a sample size of 100 will be used to ensure the correlation is estimated to a reasonable precision. The 95% confidence interval for a Pearson correlation of 0.9 would be [0.86, 0.93] and for a correlation of 0.80 [0.73, 0.85].

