#### Does case finding or screening produce better results?

Within the Intervention group, the patient outcomes for the group with memory complaints or identified by the GP as having possible or probable dementia (case finding group) will be compared with outcomes for the group without memory complaints or identified memory problems (screening group). Acceptability of the process and satisfaction with care will be particularly examined, both from a quantitative and a qualitative point of view. The performance of the GPCOG in the case finding and screening groups will be compared. In particular positive predictive value, negative predictive value and misclassification rates will be compared. GP audits will be examined to determine how many patients in each group would have a missed diagnosis of dementia if the GPCOG had not been administered.

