#### Test parameters of the GPCOG

The GPCOG will be compared with the DSM diagnosis derived from the CAMCOG as a 'gold standard', and sensitivity, specificity, positive predictive value, negative predictive value and misclassification rate will be calculated. ROC curve analysis will be employed to examine the discrimination ability of the GPCOG test (i.e. ability to detect dementia) relative to MMSE. This is important as the MMSE is now commonly used in General Practice. GPCOG test-re-test and inter-rater reliability (between the nurse and the GP) will be calculated, using the kappa coefficient and intra-class correlation coefficient.

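### Comparing the GPCOG between case-finding and screening patients by PPV and NPV mixes test performance with prevalence; sensitivity and specificity by group should be added

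*Protocol article*

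**What the plan says.** The section *Does case finding or screening produce better results?* states: "The performance of the GPCOG in the case finding and screening groups will be compared". The next sentence picks out the measures: "In particular positive predictive value, negative predictive value and misclassification rates will be compared". Sensitivity and specificity are not named there.

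The groups are defined under *Case finding and screening*. A patient enters the case-finding group by having raised memory complaints with the GP, intending to raise them, or having sought treatment or remedies for memory. A second route is the GP's own suspicion: "Patients identified as having possible or probable dementia on the GP baseline audit" are included as well. Everyone else is a screening patient.

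Under *Test parameters of the GPCOG*, "sensitivity, specificity, positive predictive value, negative predictive value and misclassification rate will be calculated", together with an ROC analysis against the MMSE. That section treats the GPCOG as a whole and does not mention the two groups. Nowhere does the article say that the between-group comparison will be read in the light of each group's prevalence.

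**The concern.** PPV and NPV depend on how common the condition is as well as on the test. The rules that form the two groups select on signs of possible dementia, so prevalence should be higher in the case-finding group. A difference in PPV or NPV would then appear even if the GPCOG detected and excluded dementia equally well in both groups. Presented under the label of performance, it could be taken as evidence that the test behaves differently in unselected patients.

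This matters because the article treats screening versus case finding as an open policy question. The Background already gives low prevalence, and the false positives it brings, as the usual argument against screening. A PPV gap would partly return that premise as though it were a result about the test.

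**Working it through.** **Inputs from the article.** Overall prevalence: "Based on a dementia prevalence of approximately 10% in over 75 year old Australians" (*Sample size*). Recruitment target 2,000; allocation 2:1; dropout 10% a year. The article's yield figures reproduce: 2,000 × 0.10 = 200 with dementia; 200 × 0.9 = 180 at 12 months; 180 × 0.9 = 162 at 24 months. It states no sensitivity, specificity, PPV, NPV or group-specific prevalence, so there is no figure of its own for this comparison to check.

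**Assumptions.** Sensitivity (Se) and specificity (Sp) are set equal in the two groups. Group prevalences p are varied so that they average 10% overall.

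**Formulas.**
- PPV = Se·p / [Se·p + (1 − Sp)(1 − p)]
- NPV = Sp(1 − p) / [Sp(1 − p) + (1 − Se)p]
- Misclassification = (1 − Se)p + (1 − Sp)(1 − p)

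**Worked case.** Se = Sp = 0.85, groups of equal size, prevalence 17% and 3% (mean 10%).
- PPV, case finding: 0.1445 / (0.1445 + 0.1245) = 0.537
- PPV, screening: 0.0255 / (0.0255 + 0.1455) = 0.149
- NPV, case finding: 0.7055 / (0.7055 + 0.0255) = 0.965
- NPV, screening: 0.8245 / (0.8245 + 0.0045) = 0.995

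**Range** (case finding vs screening):

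| Se / Sp | Prevalence | PPV | NPV | Misclassification |
|---|---|---|---|---|
| 0.85 / 0.85 | 17% vs 3% | 53.7% vs 14.9% | 96.5% vs 99.5% | 15.0% vs 15.0% |
| 0.85 / 0.80 | 26.7% vs 2.9% | 60.7% vs 11.1% | 93.6% vs 99.5% | 18.7% vs 19.9% |
| 0.85 / 0.80 | 16% vs 4% | 44.7% vs 15.0% | 96.6% vs 99.2% | 19.2% vs 19.8% |
| 0.85 / 0.80 | 16.7% vs 7.1% | 45.9% vs 24.6% | 96.4% vs 98.6% | 19.2% vs 19.6% |
| 0.85 / 0.80 | 10% vs 10% | 32.1% vs 32.1% | 98.0% vs 98.0% | 19.5% vs 19.5% |

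Rows 2 and 4 put 30% of patients in the case-finding group, with 80% and 50% of the dementia cases respectively. Row 3 uses equal groups with 80% of cases in case finding. In every row the difference in sensitivity and in specificity is zero.

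**Misclassification.** The group difference equals |Se − Sp| times the prevalence difference. It is zero when Se = Sp. At 0.80/0.90 with 17% vs 3% it is 0.10 × 0.14 = 1.4 points (11.7% vs 10.3%).

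**Chance of a nominally significant PPV difference.** Assume the comparison uses Intervention patients, about 2,000 × 2/3 = 1,333. With Se 0.85, Sp 0.80 or 0.85, and the prevalence pairs of rows 2 to 4, a two-sided 5% test that ignores clustering finds a PPV difference with probability 0.97 to 1.00, although the test is identical in both groups.

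**Precision of the added measures.** Equal groups give 1,333 / 2 ≈ 667 screening patients. At 3% prevalence, 667 × 0.03 ≈ 20 have dementia, and a sensitivity of 0.85 has a 95% half-width of 1.96 × √(0.85 × 0.15 / 20) ≈ 0.16. Specificity, on about 647 patients, has 1.96 × √(0.85 × 0.15 / 647) ≈ 0.03. Both are before clustering.

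**The case against.** The section heading asks which strategy gives better results. The Background explains the interest: false positives, distress and burden when a low-prevalence population is screened. For that question the predictive values at each group's own prevalence are the right quantities. This stands, and they should not be removed.

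A reader might infer that the plan rules out group-specific sensitivity and specificity. It does not. The naming sentence gives emphasis to three measures without excluding others, the preceding sentence plans a general comparison of performance, and the 2x2 tables will exist. What remains is that the article chooses which measures to emphasise for a comparison of performance, and none of those chosen isolates the test from the prevalence.

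A reader might also infer that all three named measures must differ between the groups. The arithmetic does not support that for misclassification, which is unchanged when sensitivity equals specificity and otherwise shifts only slightly.

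Nor do the figures support the view that the comparison would uniformly count against screening. PPV is lower there, NPV is higher, and misclassification can move either way (lower in screening at 0.80/0.90, slightly higher at 0.85/0.80).

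Finally, *Sample size* assumes about half the participants fall in each group, in a passage about patients with dementia. If both all patients and dementia cases split 50:50, prevalence is 10% in each group and nothing differs. That would require memory concerns and GP suspicion to carry no information about dementia, which is implausible.

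**Conclusion.** The point holds in a limited form. As worded, the comparison of GPCOG performance leads with PPV and NPV, which would very probably differ between the groups because of how the groups are formed. Over the unequal-prevalence scenarios shown, an identical test gives a PPV gap of about 21 to 50 percentage points and an NPV gap of about 2 to 6 points.

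These sizes rest on assumed sensitivity, specificity and group prevalences, since the article gives only the overall 10%. The direction rests on prevalence being higher in the case-finding group, which the definitions make very likely but do not guarantee.

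The point concerns aim 2. It does not touch the primary outcomes, the randomisation or the data collected.

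**What to change.** In *Does case finding or screening produce better results?*:

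1. Add sensitivity and specificity (or likelihood ratios) of the GPCOG by group, with confidence intervals that allow for clustering by practice, as the measures of whether the test itself performs differently.
2. Keep PPV, NPV and misclassification, report them beside each group's observed prevalence, and describe them as the practical yield and false-positive burden of each strategy.
3. State that the sensitivity comparison will be reported as an estimate with its interval, because there may be few dementia cases among screening patients.

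The cost is a few sentences and a small amount of extra analysis. No new data are needed, as the same 2x2 tables supply every figure. The drawback is the imprecision shown above: specificity by group should be well estimated, but sensitivity in the screening group may not be, and an inconclusive result there should not be read as equal performance.

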#### Test parameters of the GPCOG

The GPCOG will be compared with the DSM diagnosis derived from the CAMCOG as a 'gold standard', and sensitivity, specificity, positive predictive value, negative predictive value and misclassification rate will be calculated. ROC curve analysis will be employed to examine the discrimination ability of the GPCOG test (i.e. ability to detect dementia) relative to MMSE. This is important as the MMSE is now commonly used in General Practice. GPCOG test-re-test and inter-rater reliability (between the nurse and the GP) will be calculated, using the kappa coefficient and intra-class correlation coefficient.

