**Methods:**

The study is a cluster randomised trial, conducted across three states and five sites. All GPs will complete an audit of their consenting patients aged 75 years or more at three time points - baseline, 12 and 24 months. GPs allocated to the intervention group will receive two educational sessions from a peer GP or nurse, and will administer the GPCOG to consenting patients at baseline and 12 months. The first education session will provide information about dementia and the second will provide individualised feedback on audit results. GPs in the waitlist group will receive the RACGP Guidelines by post following the 12 month audit

Outcomes: Primary outcomes are carer and consumer quality of life and depression. Secondary outcomes include: rates of GP identification of dementia compared to a more detailed gold standard assessment conducted in the patient's home; GP identification of differential diagnoses including reversible causes of cognitive impairment; and GP referral to specialists, Alzheimers' Australia and support services. A "case finding" and a "screening" group will be compared and the psychometrics of the GPCOG will be examined.

Sample size: Approximately 2,000 subjects aged 75 years and over will be recruited through approximately 160 GPs, to yield approximately 200 subjects with dementia (reducing to 168 by 24 months).

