### Aims of the study

1. Compared to a GP group which does not receive peer delivered education, to examine whether training in and use of a dementia screening instrument and relevant information (see *The Intervention *section below) improves:

i. GP identification (diagnosis) of dementia

ii. Distinction by GPs between dementia and other diseases, including depression (hereafter termed "differential diagnosis")

iii. GP elimination of reversible causes of cognitive impairment

iv. Active management of dementia by GPs as evidenced by increased referral to appropriate services, to Alzheimer's Australia and/or to medical specialists for memory problems where indicated.

Outcomes for consumers and their support people in terms of quality of life (primary outcome), depression (primary outcome), satisfaction with care, and access to Alzheimer's Australia, appropriate services or specialists when indicated.

2. To determine whether a screening or a case finding approach to dementia results in:

i. better outcomes for people with dementia and their carers

ii. a more acceptable process for consumers, support people and GPs

3. o test the psychometric properties of the GPCOG including inter-rater reliability, test-retest reliability and comparison with the MMSE..

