### Data collection

#### Patient assessment

The research nurse will use a laptop computer to collect demographic data from all consenting patients and to administer the GPGOG, CAMCOG, GDS, WHOQOL-BREF, GPAQ and ADL (for patients in CAMCOG dementia range only). Patients will be asked about any memory-related services accessed, referral to Alzheimer's Australia, and referral to a specialist for memory problems. The research nurse will compile a list of all prescription and over the counter medications currently used by the patient, so that medication can be excluded as a cause of cognitive impairment. Complementary and alternative medicines will be included. In addition the nurse will perform a "75 + Health Assessment" rebateable under the Australian Medicare system on eligible patients where this has been requested by the GP. These data will not be used by the study, but are returned to the GP for his or her use. This part of the assessment is a provided as a service to the GP. Brief questions used in our previous research will be used to measure the acceptability of the interview process. We will ask patients to send answers back in a reply-paid envelope, to avoid bias due to the presence of the nurse. At the completion of the assessment the nurse will hand the patient a sealed envelope. In the case of patients in the intervention group, it will direct the patient to obtain an appointment with his/her GP as soon as possible to follow up on the 75+ Health Assessment and to have the GPCOG re-administered. In the case of patients in the waitlist group, it will suggest a follow up for the 75 Plus Health Assessment only. Patients will be reassessed using the same instruments at 12 and 24 months after baseline interviews.

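### The nurse-GP GPCOG coefficient measures combined rater-and-occasion reproducibility, not the inter-rater reliability that the third aim lists separately

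*Protocol article*

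**What the plan says.** All references are to the protocol article.

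- **Aims of the study.** The third aim is to "test the psychometric properties of the GPCOG including inter-rater reliability, test-retest reliability and comparison with the MMSE". Inter-rater and test-retest reliability are listed as two properties.
- **Test parameters of the GPCOG.** "GPCOG test-re-test and inter-rater reliability (between the nurse and the GP) will be calculated, using the kappa coefficient and intra-class correlation coefficient". The form of the ICC is not given.
- **Patient assessment, first score.** The research nurse will "administer the GPGOG, CAMCOG, GDS, WHOQOL-BREF, GPAQ and ADL" (the first item is the GPCOG, misspelt).
- **Patient assessment, second score.** At the end of that visit an intervention patient receives a sealed envelope, and "it will direct the patient to obtain an appointment with his/her GP as soon as possible", among other things "to follow up on the 75+ Health Assessment and to have the GPCOG re-administered". For a waitlist patient, "it will suggest a follow up for the 75 Plus Health Assessment only".
- **Abstract, Methods.** Intervention GPs "will administer the GPCOG to consenting patients at baseline and 12 months". No interval from the nurse's test is given there either.
- **Sample size.** A sample of 100 is set for test-retest reliability, with example confidence intervals for Pearson correlations of 0.9 and 0.80. No sample size or target is given for inter-rater reliability.

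**The concern.** Inter-rater reliability asks how far two raters agree about the same performance, or at least about the same patient in the same state. Test-retest reliability asks how far a patient's score holds between occasions. On the procedure described, the nurse and the GP do not score one session: the GP gives the test afresh at a later appointment. Every nurse-GP difference then carries rater and occasion variation together, and one coefficient cannot divide them.

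Three features make the figure harder to read:

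- The order is always nurse then GP, so any practice effect falls on the GP's score and looks like a rater difference.
- The interval depends on when the patient books and attends.
- Pairs come only from the intervention arm, and only from patients who act on the letter.

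The article notes that the refined GPCOG has not been tried in a large random sample of GP patients, so coefficients from this trial may be relied on. A figure published as inter-rater reliability would then be taken for a property that was not measured.

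**Working it through.** **1. The plan's own reliability figures.** The only ones are the intervals under Sample size: [0.86, 0.93] at r = 0.9 and [0.73, 0.85] at r = 0.80, n = 100, labelled 95%. Fisher's z gives tanh(atanh(r) ± 1.96/√97), with 1.96/√97 = 0.199:

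- r = 0.9: tanh(1.472 ± 0.199) = [0.855, 0.932]
- r = 0.80: tanh(1.099 ± 0.199) = [0.716, 0.861]

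The printed limits match 90% intervals instead ([0.863, 0.927] and [0.731, 0.853]). This labelling slip is a separate matter and does not bear on the present point. There is no inter-rater figure to reproduce.

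**2. What a nurse-GP pair contains.**

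| Feature | Same-session inter-rater design | Nurse-GP pair as described |
|---|---|---|
| Rater | differs | differs |
| Occasion | same | differs |
| Order | not applicable | nurse first |
| Interval | none | not fixed |
| Who contributes | as sampled | intervention patients who attend |

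**3. Effect of occasion variance (illustration).** Set between-patient variance to 1, rater and scoring error variance to e, and occasion variance to o. Let R = 1/(1 + e) be the nominal inter-rater value with no occasion variance.

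- Both raters score one session: (1 + o)/(1 + o + e), because occasion variance is shared.
- Raters score different occasions: 1/(1 + o + e).

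The documents give neither e nor o. The assumptions are R = 0.90 (e = 0.111) or R = 0.80 (e = 0.25), with o from 0.05 to 0.20 and independent errors.

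| R | o | One session | Different occasions |
|---|---|---|---|
| 0.90 | 0.05 | 1.05/1.161 = 0.90 | 1/1.161 = 0.86 |
| 0.90 | 0.10 | 1.10/1.211 = 0.91 | 1/1.211 = 0.83 |
| 0.90 | 0.20 | 1.20/1.311 = 0.92 | 1/1.311 = 0.76 |
| 0.80 | 0.05 | 1.05/1.30 = 0.81 | 1/1.30 = 0.77 |
| 0.80 | 0.10 | 1.10/1.35 = 0.81 | 1/1.35 = 0.74 |
| 0.80 | 0.20 | 1.20/1.45 = 0.83 | 1/1.45 = 0.69 |

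**4. Effect of a uniform practice gain.** A shift of d between-patient SDs leaves a consistency ICC unchanged. An absolute-agreement ICC becomes 1/(1 + e + o + d²/2). At R = 0.90 and o = 0.10:

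- d = 0.3: 1/(1.211 + 0.045) = 0.80
- d = 0.5: 1/(1.211 + 0.125) = 0.75

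Because the ICC form is unstated, it is open whether this applies.

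**5. Effect of carry-over.** If a share c of the error and occasion variance is common to both administrations (remembered answers, for instance), the coefficient is (1 + c(e + o))/(1 + e + o). At R = 0.90 and o = 0.10:

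- c = 0.25: 0.87
- c = 0.50: 0.91

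It reaches the nominal 0.90 at c of about 0.43, and the one-session value at c = o/(e + o) = 0.10/0.211 = 0.47. At R = 0.80 and o = 0.10 the corresponding shares are about 0.23 and 0.10/0.35 = 0.29. The direction is therefore not fixed by the design.

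**The case against.** The strongest reply is that this is a condensed article. Patient assessment describes the general patient pathway, and the full protocol may describe a reliability substudy in which both raters score one session. The sample of 100 for test-retest hints at something of the kind. It can be added that the article openly names the nurse and the GP and says the test is given again, so nothing is hidden, and that only one coefficient under a third aim is involved.

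Part of this stands. A substudy cannot be ruled out, and the primary outcomes, the main sample size and the comparison of arms are untouched. But the point rests on what the article states, not on what it omits. It names the rater pair, calls the result inter-rater reliability, and describes how the two scores arise. If another procedure supplies the inter-rater figure, the sentence under Test parameters of the GPCOG still needs to say so.

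A reader might infer more than the documents support:

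- **That the coefficient will certainly be too low.** Occasion variance pushes it down, but carry-over could offset or reverse that, and a uniform practice gain lowers only absolute agreement.
- **That the bias can be computed from the plan's own values.** Combining retest values of 0.90 and 0.80 with an assumed inter-rater ICC of 0.90 gives 0.9/1.111 = 0.81 and 0.8/1.111 = 0.72. The 0.9 and 0.80 are only example Pearson correlations used to show interval width, the inter-rater value is not in the documents, and the calculation leaves rater error out of the retest coefficient. If that error is independent scoring error already inside the retest figure, nurse-GP agreement simply equals the retest value, and at 0.90 for both there is no understatement.
- **That setting differs in every pair.** The patient inclusion criteria allow a home or a surgery visit.
- **That the 100 retest patients are tested twice by the same rater.** The article does not say so; they could be nurse-GP pairs.
- **That advice on practice-nurse help would go wrong.** The rater here is a research nurse.

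**Conclusion.** Wrong as written. On the procedure described, the nurse-GP kappa or ICC confounds rater with occasion, in a fixed order and at an uncontrolled interval, among intervention patients who attend. It does not measure the inter-rater reliability that the third aim sets apart from test-retest reliability. This rests on the nurse-GP pairs being those produced by the letter to intervention patients, the only source the article describes.

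The coefficient will probably be lower than same-session inter-rater reliability. The documents give no occasion variance, practice effect or carry-over, so the amount cannot be calculated; the values under working show a possible range and are not estimates. The consequence is confined to the psychometric aim.

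**What to change.** Under Test parameters of the GPCOG:

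1. Call the nurse-GP coefficient combined between-rater and between-occasion reproducibility.
2. Compute it on pairs that fall within a prespecified maximum interval between the two administrations.
3. Report the distribution of that interval, the mean nurse-to-GP score shift, and how the shift relates to the interval.
4. Claim a separate rater component only if the test-retest sample of 100 under Sample size is confirmed to be same-rater, at a comparable interval. Otherwise rater and occasion variance cannot be separated, and a variance-components model would not be identifiable.

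The cost is mainly wording and a short descriptive analysis. It requires the dates of both administrations, which the article does not mention recording. The downside is fewer usable pairs after the interval restriction and a less specific reliability claim. If an inter-rater figure proper is wanted, both raters would have to score one session in a subset; that is added fieldwork, not a change of analysis.
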